### Reliability of naïve and sensitised sensory function protocol

To determine intratester reliability, we repeated the sensory function protocol performed by the same investigator in n=12 healthy volunteers on two different occasions within 2–6 weeks. Intraclass correlation coefficients (3.1) revealed good to excellent agreement for all sensory testing variables (table 1).^38^

**Table 1 T1:** Intratester reliability of sensory function protocol

	Intraclass correlation coefficients	95% CI	P value
CDT	0.728	0.277 to 0.914	0.003
WDT	0.764	0.351 to 0.927	<0.0001
TSL	0.638	0.161 to 0.878	0.005
HPT	0.752	0.339 to 0.922	0.002
MPT	0.928	0.767 to 0.979	<0.0001
WUR	0.634	0.113 to 0.880	0.012
VDT	0.956	0.860 to 0.987	<0.0001
PPT	0.734	0.305 to 0.915	0.002
VAS	0.893	0.667 to 0.970	<0.0001
Flare area	0.610	0.095 to 0.869	0.015
Brush-evoked allodynia	0.756	0.365 to 0.922	0.001
Punctuate hyperalgesia	0.615	0.094 to 0.871	0.013
Postsensitisation MPT	0.941	0.808 to 0.983	<0.0001
Postsensitisation HPT	0.758	0.339 to 0.924	0.002

CDT, cold detection threshold; HPT, heat pain threshold; MPT, mechanical pain threshold; PPT, pressure pain threshold; TSL, thermal sensory limen; VDT, vibration detection threshold; VAS, Visual Analogue Scale; WDT, warm detection threshold; WUR, wind-up ratio.

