#### Data analysis plan

The cleaned genetic data will first be merged with reference samples worldwide, such as the 1000 Genomes Project,^17^ Simons Genome Diversity Project,^47^ Estonian Biocentre Human Genome Diversity Panel,^48^ and additional European and Native American samples that are particularly relevant for Latin American populations.^49^ The merged dataset will be checked for genetic outliers, through genetic PCs and continental ancestry proportions (using supervised Admixture^50^), and for unexpected genetic similarities. These steps can often detect any sample misplacement or contamination, which might be reflected in sex mismatch, unexpected genetic similarities or inflated heterozygosity rates.^40 51^ Genetic ancestry estimates will be compared with self-reported ancestry information (see online supplementary appendix 1), particularly for genetic outliers or samples showing unexpected results. Participants self-reporting for ethnicities rare in Colombians, such as East Asian or South Asian, would also be excluded as outliers. The authors have extensive experience in conducting association analysis in admixed populations, including several GWAS publications on a wide range of phenotypes which contain detailed protocols on how to conduct such analyses.^27 39 52 53^ Further details of the currently used quality control protocol for CANDELA samples^53^ are provided in online supplementary appendix 2.

The genetic data allow estimation of the narrow-sense heritability of any quantitative trait, which is the fraction of trait variance that is explained by the genetic data. Estimates of heritability, obtained using the software GCTA,^54^ will provide an idea of which traits have more of a biological basis versus which are more environmentally determined, and thus which traits would be more amenable to genetic analysis for discovery of associated genetic variants. Note however that relatively precise estimate (low SDs) of heritability by this method requires several thousand samples,^52^ so the currently proposed sample size might be underpowered to estimate heritability accurately.

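### Differences in trait heritability cannot be read as biology versus environment while Table 1 repeatability runs from 0.610 to 0.956

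*Protocol article*

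**What the plan says.** The Data analysis plan defines narrow-sense heritability as a proportion of trait variance, "which is the fraction of trait variance that is explained by the genetic data". It says that the GCTA estimates "will provide an idea of which traits have more of a biological basis versus which are more environmentally determined", and draws a second inference from them: "and thus which traits would be more amenable to genetic analysis for discovery of associated genetic variants". The one reservation concerns precision: a tight estimate needs several thousand samples, "so the currently proposed sample size might be underpowered to estimate heritability accurately".

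The section on reliability of the sensory protocol reports ICC(3,1) for 14 variables, from 12 healthy volunteers tested twice by the same investigator 2–6 weeks apart. The lowest and highest rows of Table 1 are "Flare area 0.610 0.095 to 0.869 0.015" and "VDT 0.956 0.860 to 0.987 <0.0001". The text rates agreement as good or better for every variable. Nothing links these reliabilities to the heritability comparison.

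**The concern.** Under the article's own definition, the denominator of heritability is all the observed variance, and each participant is measured at a single appointment. Anything that varies within a person from one occasion to the next (instrument noise, rating noise, transient state) enters that denominator and lowers the estimate. Two traits with the same genetic basis but different repeatability will give different heritabilities. The plan would read the lower one as more environmental.

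Table 1 shows that the traits do differ in repeatability. At the low end are flare area (0.610), punctate hyperalgesia (0.615), wind-up ratio (0.634) and thermal sensory limen (0.638). At the high end are mechanical pain threshold (MPT, 0.928), post-sensitisation MPT (0.941) and VDT (0.956). What is at stake is a wrong statement about individual traits. The Introduction stresses that heritability varies greatly between sensory modalities, so readers will look for such comparisons.

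**Working it through.** **Inputs.** ICCs and confidence intervals: Table 1. Reliability sample of 12, two occasions: same section. Upper heritability of 0.55: Introduction, an upper figure from twin studies. GWAS sample of 1500–2000: sample size section. Heritabilities of 0.25 and 0.10 are assumptions, used to show a range.

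**1. Consistency of Table 1.** The ICCs cannot be recomputed without raw data, but their intervals can be checked. With two occasions, F = (1 + ICC)/(1 − ICC); the limits follow by dividing and multiplying F by the 97.5% point of F(11, 11) and transforming back.
- Flare area: F = 1.610/0.390 = 4.13, giving 0.086 to 0.870 (stated "0.095 to 0.869").
- VDT: F = 1.956/0.044 = 44.5, giving 0.855 to 0.987 (stated "0.860 to 0.987").

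Across all 14 rows the limits agree within about 0.03, so the table is credible as printed.

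**2. Attenuation.** If the additive genetic variance lies in the stable part of the trait, then observed h² = (genetic variance / stable variance) × (stable variance / total variance) = stable-trait h² × ICC.

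| Stable-trait h², equal for all traits | VDT | MPT | Heat pain threshold | Flare area | VDT − flare |
|---|---|---|---|---|---|
| 0.55 | 0.526 | 0.510 | 0.414 | 0.336 | 0.190 |
| 0.25 | 0.239 | 0.232 | 0.188 | 0.152 | 0.086 |
| 0.10 | 0.096 | 0.093 | 0.075 | 0.061 | 0.035 |

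The ratio does not depend on the assumed heritability: 0.610/0.956 = 0.64, or 0.956/0.610 = 1.57 the other way round. The proportional loss per trait runs from 1 − 0.956 = 4% to 1 − 0.610 = 39%.

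**3. Does this tilt against sensitised traits?**
- Naïve (eight traits): (0.728 + 0.764 + 0.638 + 0.752 + 0.928 + 0.634 + 0.956 + 0.734)/8 = 6.134/8 = 0.767.
- Sensitised (six traits): (0.893 + 0.610 + 0.756 + 0.615 + 0.941 + 0.758)/6 = 4.573/6 = 0.762.
- Same test before and after mustard oil: MPT 0.928 and 0.941; heat pain threshold 0.752 and 0.758.

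There is no overall tilt, and the like-for-like pairs lean very slightly the other way.

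**4. Size against sampling error.** The standard error of a GCTA estimate is roughly √(2/(N² × v)), where v is the variance of the off-diagonal relatedness values. The article does not give v; I assume 2×10⁻⁵ to 2×10⁻⁴.
- N = 1500, v = 2×10⁻⁵: √(2/45) = 0.21. N = 2000, v = 2×10⁻⁴: √(2/800) = 0.05.
- For a difference between two traits, treated as independent, multiply by √2: 0.298 and 0.071.
- The gap of 0.190 is then 0.6 to 2.7 standard errors; the gap of 0.086 is 0.3 to 1.2.

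**5. The discovery inference.** At 5×10⁻⁸ and n = 1500, 80% power needs a marker explaining about 2.6% of observed variance. As a share of stable variance, that is about 4.2% at an ICC of 0.610 and 2.7% at 0.956. Low repeatability reduces GWAS power too, so uncorrected heritability is the right guide to which traits suit discovery.

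**The case against.** The strongest case against the point is that it concerns one hedged sentence. The article promises only an indication, warns that the estimates may be inaccurate, and runs the GWAS on every trait whatever its heritability. The ICCs rest on 12 people and are wide; even the two extreme intervals just overlap (upper limit 0.869 for flare area, lower limit 0.860 for VDT). A rough Fisher-z comparison of those two gives z = 2.7, p about 0.006. It treats the ICCs as independent and takes the minimum and maximum of 14, one of 14×13/2 = 91 pairs, so the ratio of 1.57 is probably inflated. A retest at 2–6 weeks also picks up real within-person change, part of which is fairly called environmental.

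All of this stands, and it limits the size of the point. It does not rescue the inference. The precision caveat describes error that shrinks with more participants, whereas attenuation stays at any sample size. Instrument and rating noise is not environmental determination.

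Four stronger readings may tempt a reader, and the article supports none of them:
- **Sensitisation would look environmental compared with naïve sensitivity.** Setting flare and punctate areas against MPT and VDT suggests this, but the means over all 14 rows are practically equal, and wind-up ratio and thermal sensory limen, also low, are naïve tests.
- **Measurement error will pass for absence of a genetic basis.** Attenuation is proportional, at most 39% on the point estimates; it can distort a ranking but does not remove heritability.
- **The inference about discovery is wrong as well.** It is valid on the observed scale.
- **Every estimate should be divided by its ICC before comparison.** For flare area, an illustrative observed value of 0.20 gives 0.20/0.869 = 0.23 to 0.20/0.095 = 2.1 across the ICC limits, which is of no use as a basis for comparison.

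**Conclusion.** The point holds in a limited form. Reading between-trait differences in GCTA heritability as biology against environment is not justified, because the estimate also falls with unrepeatability, and Table 1 indicates that traits differ in this. On the point estimates, equal stable-trait heritability would leave flare area at about 0.64 times VDT, a gap of 0.19 at 0.55 and 0.09 at 0.25.

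This assumes that the genetic variance sits in the stable part of each trait and that the pilot ICCs carry over to the GWAS sample. With 12 volunteers the second assumption is weak, so the direction is firmer than the size, and sampling error in the heritability estimates may hide the effect. The consequence is a possible wrong conclusion about individual traits. The association tests, their thresholds and the sample size do not depend on it.

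**What to change.** Keep uncorrected heritability as the guide to which traits are amenable to discovery. Replace the contrast between biology and environment with a statement along these lines: *Observed heritability reflects both genetic variance and the repeatability of the measurement; a low value is therefore not by itself evidence that a trait is environmentally determined.* Report each GCTA estimate, with its standard error, beside the trait's Table 1 ICC and confidence interval. Show h²/ICC at most as a sensitivity display, with the ICC uncertainty made plain, and not as the basis for comparing traits.

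The cost is one reworded sentence and one more table column from figures already published in the article. The price in interpretation is weaker statements about differences between traits.

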#### Handling of missing data

It might not be possible to record some traits in some individuals, even though the completeness of the first 100 samples suggests that missingness will be low. The single-trait methods used in traditional GWAS analyses automatically exclude individuals from the analysis of a trait who have missing values for that trait. The same applies to individuals having missing genotypes for any particular SNP. However, genotyping success rate using the Illumina HumanOmniExpress chip in the CANDELA cohort is very high (>99.8%), so the number of excluded individuals in any analysis would be very low overall.

Some multivariate analyses such as PCs when applied on the set of phenotypes require having recorded values of all phenotypes for an individual. Instead of using the subset of individuals who have the complete set of phenotypes recorded, which would incur some loss in sample size, the missing phenotype data for each individual will be imputed following standard statistical procedures as implemented in the R package ‘mice’.^62^ When the proportion of missing data is small, imputation is preferable in such multivariate analyses than sample exclusion, and is routinely applied to genetic data such as while calculating genetic PCs.^58^

## Discussion

This GWAS including a well-defined cohort of healthy participants will provide important insights into the genetic aspects underlying experimental pain sensitivity in the naïve and sensitised state. This may allow further exploration of potential biological mechanisms underlying pain sensitivity. Future studies will be required to extrapolate these findings to patient populations with chronic pain.

### Patient and public involvement

No patient involvement is performed during this study.

### Ethics and dissemination

Findings will be disseminated to commissioners, clinicians and service users via papers and presentations at international conferences such as the biennial World Congress of International Association for the Study of Pain. We will also post our findings to the publicly available painnetworks.org database.
